### Sample size {14}

Sample size justification:

The power analysis for the primary outcome is based on the following results:

• A study comparing 18F-DOPA influx between FM participants (*N* = 6) and a healthy control (*N* = 8) group [74, 75] yielded a mean effect size of 1.17; using this effect size, a power analysis with G*Power [19] showed that a group of 12 participants is optimal to obtain significant results with *T*-test comparing 18F-DOPA uptake between FM and healthy participants at baseline. We would round up to 20 to accommodate for technological problems, as the first measures will be done in healthy participants.

• Garland et al. [32] found significant neurophysiological changes after MORE treatment with EEG measure in 29 participants (F1,26 = 4.47; ηpartial^2^ = .15) in response to reward before and after the MORE intervention in chronic pain patients with sample sizes of *N* = 11 (active group) and *N* = 18 (support group). Using this effect size, a power analysis with G*Power [19] showed that 14 participants are necessary for an ANOVA with 2 factors and repeated measures to be significant. However, results obtained with EEG cannot be directly compared to PET measures, and there are so far no available studies with FDOPA in that context.

The power analysis for the secondary outcomes is based on the following results:

• A randomized controlled study of the MORE intervention by Garland et al. [26, 31] evidenced significant reductions in self-reported pain severity with medium effect size (Cohen’s *d* = 0.5, effect size *F* = 0.46) after the MORE intervention in a starting group of 115 participants and of 69 at post-intervention measures (*N* = 31 for MORE and *N* = 38 for support group). Based on these estimates, an ANOVA to be significant should have a minimal sample of *N* = 20 participants after treatment in each group.

• A randomized controlled study by Garland et al. [33–35] found significant effects of MORE on self-reported pain, stress, and positive affects in daily life (with AA measures) in a group of *N* = 30 using multilevel analyses, with effect sizes yielding to a minimal sample of 20.

• In their randomized clinical trial of the MORE intervention in chronic pain patients with opioid abuse, [26, 31] found a 20% drop-out between the beginning and completion of the intervention.

• In order to have a sample size sufficient to obtain significant results for the primary outcomes (FDOPA) and clinical pain measures as well as for the secondary outcomes (in particular daily life measures), we consider a minimal sample of *N* = 20 in each FMS group. Considering a 20% drop-out in total yields to a starting sample of 25 participants in each FMS group (MORE and non-intervention control). To account for data loss related to technical problems as well as for the average size of the MORE group of *N* = 8, we will round up to *N* = 32 in each FMS group.

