## Discussion

Among chronic pain conditions, FM is a frequent and very disabling disease, which is still poorly understood and difficult to treat. This project aims to investigate if the mindfulness-based MORE intervention is able to restore the DA function in FM patients, in particular with regard to DA responses to reward, and to reduce pain and mood symptoms. More specifically, we expect the FM participants to show altered DA responses to reward before MORE compared to healthy controls, and we expect these alterations to be reduced after the MORE intervention compared to a non-intervention control group. Building on a previous project of our group pointing to a dysfunction of the DA system in FM [49], we will extend here the understanding of the role of DA in FM and investigate the potential of a non-pharmacological intervention to decrease pain and ameliorate mood in FM as well as to induce changes in the central DA function. With regard to the clinical effects of MORE, [26, 31] found a medium effect size of the intervention on pain severity. We used their effect size to calculate the size of our sample for the primary outcome of DA responses to monetary reward and are confident that the use of a multi-modal design combining clinical and AA measures will permit a better detection of the effects. At a clinical level, the use of standardized outcomes recommended for the study of FM will allow us to target clear variables for changes associated with the intervention. Using a non-intervention control design instead of a design with an active control group might increase the effects as we will not control for placebo effects. However, the justification is based on ethical and methodological reflections that have been discussed in the design section, and constitute for this sample with these specific measures is the state-of-the-art. We are aware that proper AA analyses need larger samples; however, the sample sizes calculated correspond to the main outcome and other studies in FMS studies and will allow for exploratory micro-analyses.

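### The pain effect is given as d = 0.5 and f = 0.46, which differ almost twofold; 20 per group follows only from the larger, and the figure of 14 for the repeated-measures ANOVA is wrong

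*Protocol article*

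**What the plan says.** All of this is in the protocol article.

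- **Sample size {14}, pain.** The earlier MORE trial is said to show a "medium effect size (Cohen’s *d* = 0.5, effect size *F* = 0.46) after the MORE intervention". From this, "an ANOVA to be significant should have a minimal sample of *N* = 20 participants after treatment in each group".
- **Sample size {14}, primary outcome.** An EEG study of MORE in 29 participants is cited with "F1,26 = 4.47; ηpartial^2^ = .15". A G*Power calculation then "showed that 14 participants are necessary for an ANOVA with 2 factors and repeated measures to be significant". The text adds that EEG and PET results are not directly comparable.
- **Sample size {14}, conclusion.** "In order to have a sample size sufficient to obtain significant results for the primary outcomes (FDOPA) and clinical pain measures", and for the daily-life measures, "we consider a minimal sample of *N* = 20 in each FMS group". This is inflated to 25 for 20% drop-out and rounded up to 32 for technical data loss and the MORE group size.
- **Outcomes {12}.** VRS and BPI pain scores are primary outcome 1B. The power section treats pain as the basis for secondary outcomes.
- **Discussion.** After citing the medium pain effect: "We used their effect size to calculate the size of our sample for the primary outcome of DA responses to monetary reward". A later paragraph says that drop-outs will be replaced.

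Alpha, target power, pre/post correlation and the G*Power effect-size option are not given.

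**The concern.** Two effect sizes that differ almost twofold on the usual conversion are offered as one. The minimum per arm depends on which was used, and it matches the one that does not fit the word medium. The 14 also conflicts with its own source: an effect that was only just significant in 29 participants cannot be reliably detected in 14.

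At stake is the statement that 20 per arm is sufficient. If d = 0.5 is the real planning effect, a null pain result would carry much less information than the protocol implies, and a reader would have no stated power by which to judge it.

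**Working it through.** **Assumptions.** Two-sided alpha 0.05, 80% power, equal arms. Pre/post correlation r is shown over a range because none is stated.

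**1. Reproducing the 20 per group.** One-way, two groups, noncentrality λ = f²N with 1 and N − 2 df.
- f = 0.46: N = 38 gives power 0.79 and N = 40 gives 0.81, so 20 per group. Exact match.
- f = 0.25 (d = 0.5): N = 128, or 64 per group. No match.
- f = 0.25 in a repeated-measures interaction with λ = f²N·2/(1 − r) and r = 0.5: N = 34, or 17 per group. No match.

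**2. Can d = 0.5 and f = 0.46 be one effect?** On the raw scale f = d/2 gives 0.25, and 0.46/0.25 = 1.84. On the change-score scale d_change = d/√(2(1 − r)) and f = d_change/2. Setting f = 0.46 gives r = 1 − (0.25/0.46)²/2 = 0.85. They agree only at that correlation.

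**3. Pain power at d = 0.5.** The group × time test with two time points is a t-test on change scores, with standardised difference 0.5/√(2(1 − r)).

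| r | standardised change | 20 per arm | 25 per arm | 32 per arm |
|---|---|---|---|---|
| 0.5 | 0.500 | 0.34 | 0.41 | 0.50 |
| 0.7 | 0.645 | 0.51 | 0.61 | 0.72 |
| 0.8 | 0.791 | 0.68 | 0.78 | 0.88 |

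Power of 80% requires r of about 0.85 with 20 per arm, 0.81 with 25 and 0.76 with 32.

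**4. Reproducing the 14.** f² = 0.15/0.85 = 0.176, so f = 0.42. With λ = f²N·2/(1 − r) and r = 0.5, λ = 4f²N. N = 12 gives power 0.75 and N = 14 gives 0.82. Exact match, as a total.

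**5. Why the 14 is wrong.** F/(F + df) = 4.47/(4.47 + 26) = 0.147, so the .15 is the partial eta squared of the reported F test. That F already reflects the pre/post correlation, and the factor 2/(1 − r) = 4 counts it again. As a check, F(1,26) = 4.47 has p = 0.044. The same effect in 14 participants gives F = 0.176 × 12 = 2.12 on 1 and 12 df, p = 0.17.

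**6. Using the partial eta squared as reported.** λ = f²(N − 2) or f²N; both conventions are shown.

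| N in total | power |
|---|---|
| 14 | 0.27–0.30 |
| 40 (stated minimum) | 0.71–0.74 |
| 51 (64 × 0.8 = 51.2) | 0.82–0.84 |
| 64 | 0.90–0.91 |

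Power of 80% is first reached at N = 47 (λ = f²N) or 49 (λ = f²(N − 2)).

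**The case against.** - **f = 0.46 may be the real planning effect.** If it came from an F test in the earlier trial, using it as reported gives 20 per group, by the same rule applied to the EEG effect in steps 5 and 6. Power at 32 per arm would then be 0.95. This stands as a possibility. The source is not at hand, so it cannot be said that d = 0.5 is right and f = 0.46 wrong. What remains is that the protocol gives both, calls the effect medium, and does not state the scale or correlation that would reconcile them.
- **The correlation could be high.** This also stands. The requirement of 64 per arm at d = 0.5 holds only for a post-test comparison or r = 0.5; it falls to 39 at r = 0.7 and 27 at r = 0.8.
- **The 14 does not set the sample size.** Correct. The minimum of 20 comes from the pain and daily-life calculations, and enrolment is 32 per arm. A reader might infer from the wrong 14 that the trial is too small for PET. The documents do not support that: at the protocol's own partial eta squared the planned sample exceeds 80%, and replacing drop-outs would raise the number of completers further.
- **The EEG caveat.** The protocol admits that EEG does not translate directly to PET. That concerns whether the effect carries over; it does not correct the calculation.
- **The Discussion sentence.** Since the pain-derived 20 is also applied to FDOPA in the sample-size conclusion, the sentence partly describes what was done. It still differs from the bullets that size the primary outcome from a PET comparison and the EEG study, and that use the pain effect for secondary outcomes.

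**Conclusion.** Wrong as written, in two places.

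**Pain.** d = 0.5 and f = 0.46 are not the same two-group effect unless f is on a change-score scale with a correlation of about 0.85, which is not stated. The 20 per group rests on f = 0.46. For the stated d = 0.5, power at 20 per arm runs from 0.34 (r = 0.5) to 0.68 (r = 0.8), so the sufficiency claim is unsupported for that effect. At 32 analysed per arm, 80% is reached only if r is about 0.76 or more.

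**Repeated-measures ANOVA.** The 14 should be about 47–49 in total. The shortfall for this effect exists only at the stated minimum of 40 completers, not at planned enrolment, and it presumes that the EEG effect transfers to PET.

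The reproduced figures of 20 and 14 both fit the assumed two-sided alpha of 0.05 and 80% power, which makes those assumptions plausible but does not confirm them.

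**What to change.** Keep the recruitment target and change the text.

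1. State which of d or f is the planning effect for pain and on what scale, with alpha, target power and the assumed pre/post correlation.
2. Replace the 14 with about 47–49 in total, and say that the partial eta squared is used as reported.
3. Replace the claim that 20 per arm is sufficient with power at 20, 25 and 32 per arm over a stated range of correlations. Acknowledge that pain is under-powered for d = 0.5 unless the correlation is about 0.76 or more with 32 analysed per arm. For the EEG-based effect, give power at 40, about 51 and 64 completers.
4. Reconcile the Discussion with the sample-size section on which effect sized the dopamine outcome.

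The cost is rewording and a less favourable power statement for pain if d = 0.5 is the planning effect. No extra patients, tests or outcomes are needed.

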### Recruitment {15}

Patients will be recruited from the interdisciplinary outpatient clinic for pain at the University Hospital Zurich, from the Department of Consultation-Liaison Psychiatry and Psychosomatic Medicine at the University Hospital Zurich, from the Neurology Department and interdisciplinary outpatient clinic for pain at the Canton Hospital Fribourg, from the outpatient pain clinic at the Division of Anesthesiology as well as the service of rheumatology at the Lausanne University Hospital, from private practices, and from adds on websites of the Rheumaliga, as well as patient groups such as the Fibromyalgieforum Schweiz in the German-speaking and French-speaking parts of Switzerland. The healthy controls will be recruited through ads, word of mouth, and from our previous and current studies as well. When interested participants call into one of the study telephone lines, they will be told about the study and screened for eligibility using predetermined scripts. If potentially eligible, an in-person visit (90-min duration) at the study center will be scheduled. This first visit can be the start of the study, or this start can be reported, depending on the clinical situation. At the study start, eligibility will be confirmed, consent provided, and the initial assessment completed.

## Assignment of interventions: allocation

### Sequence generation {16a}

We will use a simple randomization procedure with a blocked size of 5, 6, or 8 according to the recruitment flow. Randomization will be performed with an online program (sealed envelope, https://www.sealedenvelope.com) with the following randomization scheme: FMS MORE/FMS non-treatment control. The randomization will be performed for each group independently, before the pre-test measures by the data manager. Randomization tables will be deposited on RedCAP. There is no randomization of the healthy control groups for allocation in the PET or AA group.

### Concealment mechanism {16b}

The list is concealed by instructed office personnel in the study center of the University Fribourg, Switzerland, who is unaware of any patient information. The randomized participants will join the MORE group or non-intervention control.

### Implementation {16c}

The 64 FM participants will be assigned to the MORE treatment or to a non-intervention control condition in a randomized way. As the study progresses, participants coming off the waitlists will also be added to the ongoing groups. We will begin with one MORE group running in Zurich and in Lausanne, but will add additional groups as numbers require. For the healthy participants, we will fill first the PET group *N* = 20 and allocate the rest to the AA group.

## Assignment of interventions: blinding

### Who will be blinded {17a}

Because there is no active control group or no placebo intervention in this study, the study staff and the participants will be unblinded.

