#### Main primary outcome

1) A.18F-DOPA influx: the difference between FM patients and healthy controls at pre-test and between pre-test and post-test in FM

1) B. Measures of pain symptoms: the difference between FM patients and healthy controls at pre-test and between pre-test and post-test in FM in the scores of the 1-item Verbal Rating Scale (VRS) [70] and of the Brief Pain Inventory (BPI) [15].

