#### Main secondary outcomes

2)The percent BOLD signal change in striatal activity during the reward task: the difference between FM patients and healthy controls at pre-test and between pre-test and post-test in FM patients3)The correlation between daily practice of mindful breathing and savoring (minutes) and increased striatal activity and 18F-DOPA influx4)Changes in pain-related and other clinical outcomes: the difference between FM patients-healthy controls at pre-test and between pre-test and post-test in FM on scores of quality of life (WHOQOL Brief [62];) and mood disturbances (State-Trait Anxiety Inventory (STAI [48];), Beck Depression Inventory (BDI)-II [43], Fibromyalgia Impact Questionnaire (FIQ [7];), Pittsburgh Sleep Quality Index (PSQI; [14]), and Emotion Regulation Questionnaire (CERQ; [51])5)Effects of the MORE intervention on self-reported pain, positive affect, and stress in daily life measured with AA: the difference between FM patients and healthy controls at pre-test and between pre-test and post-test in FM patients

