### Data management {19}

All study data must be archived for a minimum of 10 years after study termination or premature termination of the clinical trial. Study data will be archived at the University Fribourg.

For data recording, we will use electronic case report forms (eCRF) from REDCap which are available at the University Hospital Zurich, University Fribourg, and at the CHUV. For each participant, an individual CRF is maintained. The CRF is coded for each participant with protocol identifier plus randomization number based on the guidelines for an acceptable coding of trial subjects available on www.swissethics.ch. Source data in this study is all information in original records, certified copies of original records of clinical findings, questionnaires, observations, or other recorded activities collected during the study only. All collected data during the study will be transferred to the participant’s CRF. Direct access to source documents will be permitted for purposes of monitoring, audits, or inspections. Access to the project plan, dataset, and statistical code, during and after the research project (publication, dissemination), will be determined by the PI. Coding will be done using participant numbers and participants will be given a number in a chronological order with the first number differentiating between healthy controls and FM participants in the screening log. Data exchange between the centers will be done using coded data. For interim and for the main analyses, the (coded) data of the study centers will be merged into one file to perform the analyses.

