#### Primary analyses

##### Main outcome 18F-DOPA

State-of-the-art image processing will be used to analyze PET and fMRI images. PET image pre-processing and analysis will be done using PMOD (PMOD software, PMOD technologies Zurich) and SPM (Wellcome Department of Imaging Neuroscience, London, UK) for the 18F-DOPA study. The most often used method to quantify biochemical function from 18F-DOPA PET image is the multiple time graphical approach (MTGA) that provides rate constants (Ki) for the storage of 18F-DOPA within regions of interest (ROIs) placed over the striatum [8] and in regions associated with the processing of reward. Images from each dynamic DOPA PET dataset will be aligned and parametric images of 18F-DOPA influx (Ki) will be created for each subject. The Ki images will be transformed into standard stereotactic space. Regional Ki values of striatal regions (putamen, caudate, nucleus accumbens) will be analyzed with statistical parametric mapping for comparison of regional Ki values on a voxel by voxel basis. Group comparisons will be tested using independent samples *T*-test for pre-test measures; treatment group × time comparisons will be analyzed with two-factorial ANOVA’s including Ki values obtained in the nucleus accumbens and the caudate to test the primary outcomes. Regional Ki values can be reported into SPSS for the main analyses and for associations with the other data. Exploratory analyses can include additional moderation and mediation analyses on the basis of the results.

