### Interim analyses {21b}

Interim analyses will include pre-test comparisons (healthy controls versus FM) on the main and secondary outcomes after completion of the first MORE group as well as exploratory pre-post comparisons on the main outcomes to control whether methodological adjustments have to be made. Data of the pre-test comparisons (healthy controls versus FM) after completion of the second MORE group will be used for first data presentation and if possible publication of pilot data.

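### The reason given for leaving study staff unblinded does not cover those who process the stored PET scans, and nothing in the protocol masks them to arm

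*Protocol article*

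**What the plan says.** The blinding section {17a} reads: "Because there is no active control group or no placebo intervention in this study, the study staff and the participants will be unblinded". It exempts nobody, and the unblinding item {17b} is answered as not applicable.

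The section on the main primary outcome lists two outcomes. The first begins "A.18F-DOPA influx: the difference between FM patients and healthy controls at pre-test" and goes on to the pre-test to post-test change in fibromyalgia patients. The second is pain on the VRS and the BPI. The fMRI measure, "The percent BOLD signal change in striatal activity during the reward task", is listed as secondary.

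The section on the 18F-DOPA analysis describes alignment of the dynamic images, parametric Ki images, transformation to standard space, a voxel-wise analysis, and regional Ki values that go into the group × time ANOVA. The section on neural responses to reward describes the MRI and fMRI processing. Neither says whether the person doing this work knows the arm.

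Data management {19} provides for coded data. The interim section {21b} allows "exploratory pre-post comparisons on the main outcomes to control whether methodological adjustments have to be made" once the first MORE group is complete.

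**The concern.** A missing placebo makes it impossible to blind the women who attend MORE and the therapists who deliver it. It places no constraint on someone working with a stored scan, who can be kept unaware of the arm whatever the comparator. The stated reason therefore does not support the stated rule for that part of the staff.

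This matters because of which outcome is affected. The Discussion concedes that self-reported pain can be influenced by knowing the allocation, and nothing in the analysis can remove that. The bias safeguard under Outcomes {12} is the use of standardised questionnaires, which does nothing for an imaging measure. 18F-DOPA influx is the primary outcome for which assessment bias could be prevented. Following {17a} as written leaves the treatment comparison on that outcome open to the criticism that scans were handled with knowledge of arm.

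**Working it through.** No figure in the plan is in dispute, so the check is a comparison of sections plus one count.

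1. **Who is unblinded, and why.** {17a} covers study staff and participants and gives one reason, the absence of a placebo or active comparator. That reason holds for participants and therapists. It has no bearing on image processing.

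2. **Is anyone masked elsewhere?** The sections on outcomes, PET acquisition, fMRI acquisition, data management, the 18F-DOPA analysis, the fMRI analysis and the interim analyses contain no statement that processing or extraction is masked. The concealment section {16b} concerns the allocation list, not the later handling of scans.

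3. **Which primary outcome could be assessed blind?** VRS and BPI are self-rated, so the rater is the unblinded participant. Ki is derived from an image by someone else. Only the latter can be masked.

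4. **Does the coding act as a mask?** It is described for confidentiality and exchange of data between centres. Under {19} the case report form code contains the randomisation number, and under {16a} the randomisation tables are stored on REDCap, which is also the data-capture system. Anyone with access to both can recover the arm. The article does not say who has that access.

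5. **Does the scan date reveal the arm?** Under the participant timeline {13}, patients allocated to MORE have their pre-test measures first, and the controls of that cohort are measured while the course is running. Within a cohort, date therefore points to arm even at baseline. The pointer is imperfect, because pre-tests for the second MORE group may begin in the same weeks as those for the first cohort's controls.

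6. **Is there room for judgement in processing?** Alignment and extraction of regional values are documented steps. The sample size section allows for data loss from technical problems, and the fMRI section allows for outliers, so someone decides which data are usable. Automation limits this room: the structural MRI pipeline is described as fully automated, the connectivity regions are atlas-based, and part of the PET analysis is voxel-wise.

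7. **How many scans are affected?** 64 fibromyalgia patients × 2 visits = 128, plus 20 healthy women × 1 visit = 20, giving 148 PET scans at full enrolment without losses. The randomised comparison uses the 128. Replacement of drop-outs, which the Discussion foresees, could raise the count.

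8. **Can the bias be sized?** No. For the group × time comparison one would need the shift in Ki caused by unmasked handling, divided by the standard deviation of the change in Ki. The document gives neither. The effect size of 1.17 in the sample size section is a standardised difference between patients and healthy women and supplies neither quantity.

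**The case against.** The strongest reply is that {17a} is one line in an article that condenses a fuller protocol supported by standard operating procedures. It says study staff and never mentions image analysts, so scan labelling may be settled elsewhere. This stands in part: a reader might infer a deliberate decision to process scans unblinded, and the article does not document one. It does not dispose of the point, because the article answers the blinding question outright, makes no exception, and gives a reason that does not fit this group.

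Other stronger readings also go beyond the text:

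- **Hand-drawn regions.** A reader might take "regions of interest (ROIs) placed over the striatum" to mean that analysts draw regions by eye. The phrase sits in a sentence about the commonly used quantification method and does not say how regions are set here.
- **The participant number.** {19} says "participants will be given a number in a chronological order with the first number differentiating between healthy controls and FM participants", in the screening log. That digit shows diagnosis, not arm, and no section says that scans carry it. It has no bearing on the randomised comparison.
- **Tuning at the interim look.** The interim section does not say that the pre-post comparisons are made by arm, or that image-processing settings would be what is adjusted. It leaves that possible and does not announce it.
- **Protection of the whole result.** Masked processing removes only bias in assessment. The Discussion accepts that placebo effects are uncontrolled, and masking would not change that.

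**Conclusion.** The point holds in a limited form. The reason in {17a} does not extend to those who process stored PET images, nor, for a secondary outcome, to those who process fMRI. No section masks them, and arm is recoverable from the randomisation number with access to the tables, or partly from scan date. The primary-endpoint consequence concerns PET only.

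A reader might go on to infer that the PET result will be biased by some stated amount. The document does not support that. The size cannot be derived, and it may be limited where processing is automated. The conclusion rests on reading study staff in {17a} as including the image analysts, since no one is excepted, and on the article's silence about masked processing elsewhere. The text should be corrected because the exposure is avoidable, affects a primary outcome and is cheap to remove. It does not invalidate the design.

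**What to change.** Reword {17a} along these lines: *Participants, therapists and recruiting staff are unblinded. Processing of PET and fMRI images, quality exclusions, and extraction of Ki and beta values are carried out masked to arm and, where feasible, to diagnosis and visit.*

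To make this work:

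- The existing data manager, who already performs the randomisation and so should take no part in processing, re-labels the scans with random codes unrelated to the randomisation number.
- Scan dates are removed from the files given to the analysts, because scan order differs by arm.
- Ki values and exclusions are locked before allocation is linked.
- Any methodological adjustment to image processing after the interim look in {21b} is decided without arm-labelled pre-post imaging results. The planned pre-test comparison of fibromyalgia patients with healthy controls can stay, as can its presentation.

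The cost is a small re-labelling effort, a paragraph of protocol text, and no early arm-level view of the imaging results. No further participants or scans are needed, and the sample size is unchanged. Because only processing changes, the step can also be applied to images already acquired but not yet processed.
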